***Overall survival and local progression-free survival.***

Overall Survival is the time between date of randomisation and date of death of any cause. Survivors will be censored on the last date known to be alive. **Local progression-free survival (local control)** will be calculated from the date of randomisation to the date of first clinical evidence of progressive disease at the primary site, or death.

Kaplan-Meier curves (Kaplan and Meier 1958) will be drawn for each treatment group. Overall survival and local progression-free survival will be compared using the Mantel-Cox version of the log rank test.

- All randomized patients treated with at least one study dose of cisplatin and etoposide will be included in the comparison of proportions of grade 3 and 4 toxicities.

**Toxicity** will be assessed according to NCI Common Terminology Criteria for Adverse Events v 3.0 (see appendix 2). The proportions of patients experiencing a grade of 3 or above acute toxicity, including acute radiation morbidity, or late radiation morbidity will be compared between the treatment groups using Chi-squared and Fisher Exact tests. Acute toxicity will be defined as toxicities occurring from commencement of treatment to 3 months after completion, late toxicity will be defined as toxicities occurring between 3 months and 2 years after completion of treatment.

### 7.3.2 Qualifications for Analysis of Tumour Response

All patients meeting the following criteria will be evaluated for tumour response and included in the analysis of tumour response rates:

- treatment with at least one dose of cisplatin and etoposide.

**Response** will be assessed according to RECIST criteria (appendix 4) and the proportion of patients in each treatment group whose best response up to, approximately 28 days post cycle 4 or, if stopped prior to cycle 4, approximately 28 days after last chemotherapy cycle given, from randomisation is complete or partial will be compared using Chi-squared and Fisher Exact tests.

### 7.4 Qualifications for Safety Analysis

Safety analyses will be performed for all randomized patients treated with at least one dose of study drug. Adverse effects will be summarized and compared between the two arms.

### 7.5 Qualifications for Dose Intensity Analysis

The relative chemotherapy and radiotherapy dose intensity will be summarised by calculating the median, standard deviation, interquartile range and range for patients in each randomised treatment group. The RDI will be compared between the treatment groups by using the Wilcoxon Rank Sum test.

Chemotherapy RDI:

Relative dose intensity (RDI) is defined as the dose intensity achieved by a patient relative to a schedule that would have given the intended PE chemotherapy on a fixed 3-weekly schedule. This is given a proportion of the fixed 3 weekly schedule and will be calculated assuming that each component of the chemotherapy schedule is equipotent. The duration of the chemotherapy for this calculation will run from the first day of chemotherapy to the last dose of the final cycle. The RDI will therefore be calculated as:

$$\frac{1}{2} \left( \frac{\text{Platinum}_{AT}}{\text{Platinum}_{PT}} + \frac{\text{Etoposide}_{AT}}{\text{Etoposide}_{PT}} \right) \left( \frac{\text{Time}_{PT}}{\text{Time}_{AT}} \right)$$

where  $\text{Platinum}_{AT}$ ,  $\text{Etoposide}_{AT}$ , are the actual total received doses and  $\text{Platinum}_{PT}$ ,  $\text{Etoposide}_{PT}$  are the respective planned total doses.

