### 4.1 CHEMOTHERAPY

Patients should start chemotherapy within two weeks of randomisation and within two weeks of a clinical assessment of fitness (section 4.1.1). Chemotherapy is cisplatin and etoposide and is given for 4 to 6 cycles. One cycle is given prior to radiotherapy. The second cycle in both arms is given concurrently with radiotherapy if possible. Radiotherapy will start on day 22 of cycle 1. In the BD radiotherapy arm, the third to sixth cycles (if applicable) are given after completion of the thoracic radiotherapy. In OD radiotherapy arm, the third & fourth cycles of PE are also given concurrently and the fifth & sixth cycles (if applicable) are given after completion of the thoracic radiotherapy.

Centres will be given the choice to stop chemotherapy after 4 cycles or to continue to up to 6 cycles. Centres who decide to give 6 cycles will have to continue doing so for all patients entered in the trial (unless it is decided that it is not in the patients best interest to receive cycle 5 and 6 or due to patient's choice)

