### 4.2.2 General radiotherapy details

Patients should be treated on a linear accelerator operating at 4-10 MV.

The total dose of radiotherapy will be

- BD arm: 45 Gy in 30 twice daily fractions of 1.5 Gy
- OD arm: 66 Gy in 33 daily fractions of 2 Gy

The total dose is prescribed at the ICRU reference point and given according to the recommendations of the EORTC radiotherapy group (25) and ICRU 50 (26). Treatment will be planned with inhomogeneity corrections.

IMRT will be permitted for the centres routinely using it for the treatment of lung cancer.

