**Radiotherapy RDI:**

Relative dose intensity (RDI) is defined as the dose intensity achieved by a patient relative to a schedule that would have given the intended radiotherapy on a fixed 45 day schedule for OD and 19 day schedule for BD. The duration of the radiotherapy for this calculation will run from the first day of radiotherapy to the last day of the radiotherapy. The RDI will therefore be calculated as:

$$\left( \frac{\text{totaldose}_{\text{AT}}}{\text{totaldose}_{\text{PT}}} \right) \left( \frac{\text{time}_{\text{PT}}}{\text{time}_{\text{AT}}} \right)$$

where  $\text{totaldose}_{\text{AT}}$  is the actual total dose received and  $\text{totaldose}_{\text{PT}}$  is the respective planned total dose received.

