Toxicity will be assessed according to NCI Common Terminology Criteria for Adverse Events V.3.0. The proportion of patients experiencing a grade of 3 or above acute toxicity, including acute and/or late radiation morbidity, will be compared between the treatment groups using  $\chi^2$  and Fisher Exact tests. Acute toxicity will be defined as toxicities occurring from commencement to 3 months after completion of treatment; late toxicity will be defined as toxicities occurring between 3 months and 2 years after completion of treatment. All patients treated with at least one dose of cisplatin and etoposide will be evaluated for tumour response and included in the analysis of tumour response rates.

Response will be assessed according to Response Evaluation Criteria In Solid Tumours (RECIST) criteria. The proportion of patients in each treatment group whose best response (up to approximately 28 days post cycle 4 or, if stopped prior to cycle 4, approximately 28 days after last chemotherapy cycle given) from randomisation is complete or partial will be compared using  $\chi^2$  and Fisher Exact tests.

Safety analyses will be performed for all randomised patients treated with at least one dose of chemotherapy. Adverse effects will be summarised and compared between the two arms. The relative chemotherapy and RT dose intensity (RDI) will be summarised by calculating the median, SD, IQR and range for patients in each randomised treatment group. The RDI will be compared between the treatment groups by using the Wilcoxon Rank Sum test.

A detailed description of patient disposition will include a summary of the following:

- ▶ All patients entered and enrolled: overall, by treatment arm and by country
- ▶ Reasons for patients entered but not enrolled
- ▶ All enrolled patients treated with study drug, by treatment arm
- ▶ Reasons patients enrolled but not treated with study drug
- ▶ Reasons patients discontinued study drug treatment
- ▶ All important protocol violations.

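### Neither relative dose intensity formula penalises stopping early, so the planned Wilcoxon comparison can favour the arm with more early stopping

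*Supplement*

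**What the plan says.** Section 7.5 of the latest protocol (version 3) defines chemotherapy RDI as the mean of the platinum and etoposide dose ratios (actual over planned), multiplied by planned time over actual time. The reference is the dose intensity achieved "relative to a schedule that would have given the intended PE chemotherapy on a fixed 3-weekly schedule". The planned dose terms "are the respective planned total doses". Actual time follows this rule: "The duration of the chemotherapy for this calculation will run from the first day of chemotherapy to the last dose of the final cycle". The symbols for planned and actual time are not defined where the dose symbols are.

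Radiotherapy RDI has the same structure. Its planned time is explicit, being taken "on a fixed 45 day schedule for OD and 19 day schedule for BD". For actual time: "The duration of the radiotherapy for this calculation will run from the first day of radiotherapy to the last day of the radiotherapy".

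Section 4.1 lets the planned course differ by centre: "Centres will be given the choice to stop chemotherapy after 4 cycles or to continue to up to 6 cycles". The planned number (4 or 6) is a minimisation factor in section 3.4, so it is known for every patient.

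The SAP gives no formula. It repeats the summary statistics and the test: "The RDI will be compared between the treatment groups by using the Wilcoxon Rank Sum test". Chemotherapy and radiotherapy dose intensity are two of the five secondary endpoints. Neither document states a cap, a floor, or a rule for patients who stop early or never start.

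**The concern.** A patient who stops early loses planned dose in the numerator but also shortens the time in the denominator, and the two largely cancel. A patient who finishes the whole course a little late keeps all the dose and is marked down for the extra days. The score therefore does not separate good delivery from truncated delivery, and can rank the truncated course higher. A patient who never starts has zero actual time, so the score is undefined and the patient leaves the comparison.

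Section 3.4 expects some patients to stop early, and section 4.7 lists toxicity, progression and patient request among the reasons, any of which may differ between arms. A rank test on this score could then report better delivery in the arm where fewer patients completed treatment.

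**Working it through.** **Check of the plan's own figures.** With a Monday start and five treatment days a week, 33 OD fractions end on day 45. From "BD arm: 45 Gy in 30 twice daily fractions of 1.5 Gy", the BD course takes 15 treatment days and ends on day 19. Both stated reference times reproduce, and a fully compliant patient scores 100%.

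**Chemotherapy, full dose, on time.** Assumption: planned time is counted from first to last dose, like actual time. K planned cycles then take 21(K − 1) + 3 days: 66 days for 4 cycles, 108 for 6. After k cycles, RDI = (k/K) × [21(K − 1) + 3] / [21(k − 1) + 3].

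- 1 of 4: 0.25 × 66/3 = 550%
- 2 of 4: 0.50 × 66/24 = 137.5%
- 3 of 4: 0.75 × 66/45 = 110%
- 4 of 4 with one 7-day delay: 66/73 = 90.4%
- 4 of 6: (4/6) × 108/66 = 109.1%

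Alternative count: 21 days per cycle in both terms. RDI = (k/K) × 21K/21k = 100% for every on-time stopper. A completer with one 7-day delay scores 84/91 = 92.3%, so the stopper still ranks higher.

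With delays (first count), a 7-day delay at every cycle gives 106.5% after 2 of 4, 83.9% after 3 of 4 and 75.9% for the completer. A stopper can fall below 100% and still outrank a completer with the same delays.

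**Radiotherapy, on schedule until the stop.** RDI = (fractions given / planned) × (19 or 45) / (calendar day of last fraction).

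| Course | Share of dose | Calculation | RDI |
|---|---|---|---|
| BD, 1 treatment day | 6.7% | (2/30) × 19/1 | 126.7% |
| BD, 20 fractions | 66.7% | (20/30) × 19/12 | 105.6% |
| BD, 22 fractions | 73.3% | (22/30) × 19/15 | 92.9% |
| BD, all 45 Gy in 22 days | 100% | 19/22 | 86.4% |
| OD, 1 fraction | 3.0% | (1/33) × 45/1 | 136.4% |
| OD, 20 fractions | 60.6% | (20/33) × 45/26 | 104.9% |
| OD, 31 fractions | 93.9% | (31/33) × 45/43 | 98.3% |

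Over all possible early stop days, BD has 8 of 14 above 100% and 6 below (lowest 92.9%). OD has 24 of 32 above, 2 at 100% and 6 below (lowest 98.3%). The low scores come from stops early in a week, just after a weekend gap.

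**Effect on the chemotherapy comparison.** The documents give no stopping rates or delays, so all of these are assumed: 266 per arm (532/2), 4 planned cycles, completers delayed 0, 7 or 14 days in total in 50%, 35% and 15%. Except where stated, stopping is 10% v 25%, after cycle 2, with the 66-day count. The table shows how often the Wilcoxon test is significant at 5% in favour of the arm with more stopping.

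| Stoppers | Favours more stopping |
|---|---|
| No delay | 87% to 88% |
| No delay, 10% v 15% stopping | 18% |
| Same delays as completers | 65% to 67% |
| Same delays, stop after cycle 3 | 23% to 27% |
| No delay, 21 days per cycle in both terms | 40% |
| 7- or 14-day delay and 20% reduction at cycle 2 | 0% (35% the other way) |

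Ranges reflect separate simulation runs. The last row reverses because those stoppers score (1.8/4) × 66/31 = 95.8% or (1.8/4) × 66/38 = 78.2%, while completers score 100%, 90.4% or 82.5%.

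If actual time may not fall below planned time, the first scenario is significant against the arm with more stopping in 88% to 89% of trials.

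**The case against.** Four points can be made for the plan.

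1. Dose intensity means dose per unit time, and completion is reported elsewhere: cycles given (7.7), reasons for discontinuing or not starting (7.6), and omissions, reductions and delays for all randomised patients (7.10). This stands in part. A reader of those summaries would see the early stopping, but they are descriptive and do not alter the planned test.

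2. A reader might infer that every early stopper scores above 100%. The documents do not support that. Six of 14 BD and 6 of 32 OD stop days score below 100%. Chemotherapy stoppers with enough delay also do: 9 days in total after 2 of 4 cycles, 4.5 days after 3 of 4. The chemotherapy percentages above 100% also need the 66-day count, and the 550% figure comes from a 3-day denominator.

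3. A reader might infer that the arm with more stopping will look better treated. That is not established either. It is what happens in most of the assumed scenarios, but the frequency varies widely and the direction reverses when stoppers have large delays and dose reductions, which is plausible for patients stopping for toxicity.

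4. Holding actual time at or above planned time has its own cost: two of 4 cycles with a 14-day delay (38 days) would score 50%, the same as two cycles on time. This stands, and is the reason to report duration separately.

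**Conclusion.** The concern holds in a limited form. As written, neither formula penalises truncation, and the SAP does not mend this. The per-patient radiotherapy scores follow from the protocol's own figures and calendar: 93% to 127% (BD) and 98% to 136% (OD) for any on-schedule early stop, against 86% for the full BD dose in 22 days. The chemotherapy scores depend on the undefined planned time: 110% to 550% for on-time stoppers of a 4-cycle course on one count, exactly 100% on the other. On both counts an on-time stopper outranks a completer delayed by one week.

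The Wilcoxon comparison can therefore favour the arm with more early stopping. How often rests wholly on assumed rates, timing and delays: with 10% v 25% stopping and the 66-day count, from about 87% of simulated trials down to about a quarter, with a reversal in one scenario.

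This should be fixed, but it is confined to two secondary endpoints. The primary overall survival analysis, the sample size and the toxicity comparison are untouched.

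**What to change.** In section 7.5 and the SAP:

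- Define planned time for chemotherapy explicitly, on the same counting rule as actual time.
- Fix planned dose at the allocated schedule: 45 or 66 Gy, and the 4 or 6 cycles planned at randomisation.
- Do not let actual time fall below planned time. An early stopper then scores no more than the share of planned dose received: for example 25%, 50% or 75% after 1, 2 or 3 of 4 full-dose cycles.
- Report percentage of planned dose and overall treatment time by arm for all randomised patients, with never-started patients at 0% of planned dose.

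The cost is a few sentences and no new data; no treatment rule changes. Reported RDI will look less favourable. Because the limit on time hides delays among early stoppers, the separate report of duration is a necessary part of the change.

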**Radiotherapy RDI:**

Relative dose intensity (RDI) is defined as the dose intensity achieved by a patient relative to a schedule that would have given the intended radiotherapy on a fixed 45 day schedule for OD and 19 day schedule for BD. The duration of the radiotherapy for this calculation will run from the first day of radiotherapy to the last day of the radiotherapy. The RDI will therefore be calculated as:

$$\left( \frac{\text{totaldose}_{\text{AT}}}{\text{totaldose}_{\text{PT}}} \right) \left( \frac{\text{time}_{\text{PT}}}{\text{time}_{\text{AT}}} \right)$$

where  $\text{totaldose}_{\text{AT}}$  is the actual total dose received and  $\text{totaldose}_{\text{PT}}$  is the respective planned total dose received.

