### 4.4 HIGH DOSE ONCE DAILY THORACIC RADIOTHERAPY

#### 4.4.1 Schedule

- **66 Gy in 33 daily fractions** over a period of **45 days** (radiotherapy to start on a Monday), 5 consecutive days a week
- The optimal overall treatment time should be 45 days. Up to 47 days is a protocol deviation and should be recorded, above 47 days is a protocol violation.
- using conformal radiotherapy and 4 to 10 MV photons emitted from linear accelerators.

- Thoracic radiotherapy will start on cycle 1 day 22, if possible concurrently with the second cycle of chemotherapy (within 24 hours of day 1, cycle 2 of PE).

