#### **4.9 PATIENTS NOT MEETING THE RADIOTHERAPY PLANNING REQUIREMENTS**

If the V20 lung, dose to the spinal cord and heart do not meet the protocol requirements, the treatment decision will be left to the local investigator, as some adjustments may be necessary regarding the radiotherapy treatments. We strongly recommend that the total dose of radiotherapy is dropped to meet the normal tissue constraints.

These patients, who would have been randomised prior to the first cycle of chemotherapy, will be included in the intention to treat analysis. A subanalysis will be done excluding patients with protocol violations.

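### The relative dose intensity formulas in section 7.5 barely penalise early stopping: on-time early stoppers can score above patients who complete treatment

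*Supplement*

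**What the plan says.** Section 7.5 of the latest protocol version defines two relative dose intensities (RDI).

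- **Chemotherapy:** the mean of the platinum and etoposide dose ratios (actual total over planned total), times planned time over actual time. On duration: "The duration of the chemotherapy for this calculation will run from the first day of chemotherapy to the last dose of the final cycle".
- **Radiotherapy:** actual over planned total dose, times planned over actual time. The reference is the intended dose "on a fixed 45 day schedule for OD and 19 day schedule for BD". On actual time: "The duration of the radiotherapy for this calculation will run from the first day of radiotherapy to the last day of the radiotherapy".

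Both are summarised by median, standard deviation, interquartile range and range. The SAP repeats the test, "The RDI will be compared between the treatment groups by using the Wilcoxon Rank Sum test", and gives no formula of its own, so section 7.5 governs. Neither document sets a floor on actual time, a cap on RDI, or a rule for patients who discontinue.

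Both dose intensities are among the five secondary endpoints in section 7.1.1. Shortened treatment is foreseen. Section 4.1 lets six-cycle centres omit cycles 5 and 6 on clinical judgement or patient choice, sections 4.1.3 and 4.7 give other routes to stopping, and section 4.9 says: "We strongly recommend that the total dose of radiotherapy is dropped to meet the normal tissue constraints".

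**The concern.** The numerator and denominator cover different spans. Planned dose and planned time refer to the full course, but actual time ends whenever the patient stops. Early stopping lowers the dose ratio and raises the time ratio together, so the shortfall largely cancels and is often more than cancelled. A patient who completes treatment with a short delay is marked down; one who stops after a single on-time cycle is not.

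The Wilcoxon test works on these ranks. If early stopping or dropping of fractions differs between schedules, the arm with more of it can appear better delivered. The standard deviation and range would also be pulled by values of 5 or 6 on a scale meant to centre on 1.

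**Working it through.** **Inputs.** OD is 66 Gy in 33 fractions of 2 Gy; BD is 45 Gy in 30 fractions of 1.5 Gy, or 3 Gy per treatment day (section 4.2.2). Radiotherapy starts on a Monday and runs five days a week (4.3.1, 4.4.1). Planned radiotherapy times are 45 and 19 days (7.5). Chemotherapy is 3-weekly with etoposide on days 1–3 (4.1.2), and 4 or 6 cycles are planned (3.4).

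**Reproducing the plan's reference schedule.** Treatment day k falls on calendar day 7·floor((k−1)/5) + ((k−1) mod 5) + 1. This gives day 45 for OD fraction 33 and day 19 for BD treatment day 15, so full on-time delivery scores 1.00 in both arms.

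**Chemotherapy, stopped early with no delay.** Time for n cycles is 21(n−1)+3: 66 days for 4 cycles and 108 for 6. RDI after k of P cycles is (k/P) × Time(P)/Time(k).

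- 4 planned: (1/4)(66/3) = 5.50; (2/4)(66/24) = 1.375; (3/4)(66/45) = 1.10; all four 1.00.
- 6 planned, after 1 to 5 cycles: 6.00, 1.50, 1.20, 1.09, 1.03.
- All four cycles at full dose, one week late: 66/73 = 0.90.

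**Radiotherapy, stopped early with no interruption.** OD: (2k/66)(45/day). BD: (3k/45)(19/day), with both daily fractions given.

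| Arm | Dose given | Last day | RDI |
|---|---|---|---|
| OD | 10 Gy | 5 | 1.36 |
| OD | 20 Gy | 12 | 1.14 |
| OD | 50 Gy | 33 | 1.03 |
| OD | 52 Gy | 36 | 0.985 |
| OD | 60 Gy | 40 | 1.02 |
| BD | 15 Gy | 5 | 1.27 |
| BD | 30 Gy | 12 | 1.06 |
| BD | 33 Gy | 15 | 0.93 |

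Over all early stopping points:

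- OD is above 1 at 24 of 32, exactly 1.00 at fractions 11 and 22, and 0.98–0.995 at the other six.
- BD is above 1 at 8 of 14 and 0.93–0.99 at the other six (treatment days 6, 7 and 11–14).
- Full dose finished two days late scores 45/47 = 0.96 (OD) or 19/21 = 0.90 (BD). In each arm that is below the lowest score of any uninterrupted early stopper (0.98 and 0.93).

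**Dose cuts.**

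- Chemotherapy reductions from cycle 2 of 4, all cycles on time: 20% gives (1+3×0.8)/4 = 0.85; 25% gives 0.81; 30% gives 0.775; cisplatin 50% with etoposide 20% gives ½(0.625+0.85) = 0.74.
- Radiotherapy cut by fraction size over the full time: 60/66 = 0.91.
- Radiotherapy cut by dropping fractions: 60 Gy in 30 fractions OD 1.02; 64 Gy in 32 fractions OD 0.99; 42 Gy in 28 fractions BD 0.985.

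**Delay before stopping.** 3 of 4 cycles with 5 days' total delay: 0.75×66/50 = 0.99. 2 of 4 with 9 days: 0.5×66/33 = 1.00; with 14 days: 0.5×66/38 = 0.87.

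**No radiotherapy given.** The formula is 0/0 and undefined.

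**The case against.** **Delivery is reported elsewhere.** Section 7.6 lists reasons for discontinuation and important violations, 7.7 the number of cycles given, and 7.10 dose omissions, reductions and delays per arm. Early stopping would be visible beside the RDI, so it would be wrong to call RDI the only planned information on delivery. This stands, but those summaries are descriptive. RDI is the only delivery measure with a planned between-arm test, and it can contradict the tables next to it.

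**A kinder reading of chemotherapy time.** If planned and actual time were both counted in whole 21-day cycles, an on-time early stopper would score exactly 1.00. That removes the excess but still gives no penalty, and it conflicts with the stated end point, the last dose of the final cycle.

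**A rank test limits the damage.** Against completers at 1.00, a score of 5.50 counts no more than 1.01. Distortion of the comparison needs unequal early stopping between arms, and the documents give no rate for either. This also stands: the direction and size of any arm-level bias cannot be computed from the documents. A reader might infer from 24 of 32 against 8 of 14 that the test favours OD. It need not, because those are counts of possible stopping points, not of patients.

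**These are secondary endpoints.** True. Overall survival, its test and the sample size do not depend on RDI.

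**Conclusion.** The formulas are wrong as written for patients who discontinue. On-time early stopping of chemotherapy always scores above 1, up to 5.50 or 6.00. Uninterrupted early stopping of radiotherapy, or a total-dose cut made by dropping fractions, scores between 0.93 and 1.36, so it carries little or no penalty. This should be fixed; it does not touch the primary endpoint.

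Three stronger readings are tempting, and the documents do not support them:

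- *That dose-reduced patients score above 100%.* Reductions with all cycles, or the full radiotherapy time, given are correctly scored below 1 (0.74–0.91 in the examples). Only radiotherapy cuts made by dropping fractions can exceed 1, and some of those do not. Section 4.9 does not say how the dose is to be lowered.
- *That the least-treated patients always rank highest.* Some uninterrupted radiotherapy stops score 1 or less, enough delay removes the chemotherapy excess, and a patient with no radiotherapy has no score.
- *That cisplatin and carboplatin milligrams are added together.* Section 7.5 has one platinum term and does not say how a switch to carboplatin (allowed in 4.1.3, dosed by the AUC formula in 4.1.4) enters it. That is a gap, not a stated error. It would matter if milligrams were summed: at a GFR of 45, AUC 5 is 5×(45+25) = 350 mg, against 75×1.8 = 135 mg of cisplatin, a ratio of 2.6. Body surface area of 1.8 m² is assumed; over GFR 40–49 the ratio runs from 2.4 to 2.7.

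The scores assume no missed fractions before stopping and the same duration rule for planned and actual chemotherapy time.

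**What to change.** In section 7.5, and by reference in the SAP:

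1. Define actual time as the days from first to last dose given, plus the remaining scheduled calendar days, weekends included, of the undelivered cycles or fractions. State that planned dose is the full protocol dose. With a patient's own reduced plan as denominator and the fixed 45 days, 60 Gy in 40 days would score 45/40 = 1.125.
2. Score a patient who receives none of a modality as 0.
3. Run the Wilcoxon test on this quantity, and report delivered dose fraction and treatment time separately by arm.
4. As a clarification, compute the platinum term per cycle, relative to the protocol dose of the agent given.

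One of four cycles then has actual time 3+63 = 66 days and scores 0.25. 50 of 66 Gy on schedule has 33+12 = 45 days and scores 0.76; counting only the 8 missed treatment days would give 41 days and 0.83, so the weekend rule must be explicit. Two of four cycles with 14 days' delay score 0.5×66/(38+42) = 0.41. On-time completion stays at 1.00, and full dose one week late stays at 0.90.

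The cost is wording and a small change to the analysis program. The present formulas already need the same doses and dates, which come from the treatment form (Form A) and radiotherapy worksheet (Form C).
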